## 2. PROTOCOL SYNOPSIS

**Study Title:** A Phase 1 Trial to Evaluate the Safety, Pharmacokinetics (PK) and Pharmacodynamics (PD) of PC-6500 (Griffithsin [GRFT] in a Carrageenan [CG] Gel) in Healthy Women

**Short Title:** Safety, PK and PD of GRFT for vaginal use

**Clinical Phase:** Phase 1

**IND Sponsor:** Population Council, Inc.

**Protocol Chair:** [name]

**Sample Size:** 27 female subjects (7 in open-label single-dose period; 20 in randomized, double-blind multiple-dose period)

**Study Population:** Healthy HIV-seronegative women aged 18-49 who are sexually abstinent during the study

**Study Site:** One US site, Albert Einstein College of Medicine (Einstein), Bronx, NY

**Study Duration:** Approximately 8 days of active participation per subject in the open label (OL) period (n=7) and 45 days of active participation per subject in the randomized, placebo-controlled, double-blind period (n=20); approximately 10 months for overall accrual.

**Study Design:** In the OL safety run-in period, 7 (seven) women will receive a single 4 g dose of PC-6500 (GRFT in a CG gel) with PK assessments through 12h and a final assessment on the following day at 24h, a PD assessment 24h post-dose; and a final safety assessment one week later (Day 8). After the first 7 women have received the single dose of PC-6500 gel and all safety/PK/PD assessments have been completed, there will be a pause in recruitment while data are reviewed. Data from the OL period will inform the subsequent PK and PD assessments in the main, randomized period of the study.

The main study will enroll 20 new subjects in a randomized, placebo-controlled, double-blind design to assess safety, PK and PD of 4 g PC-6500 used once daily for 14 consecutive days. Subjects in the main study will be randomized to PC-6500 gel (n=14) or PC-535 (CG placebo) gel (n=6). Subjects will also be randomized to one of two time points (4 hours or 8 hours) for blood and cervicovaginal lavage (CVL) specimen collection after Dose 1. At baseline (at least 7 days before Dose 1) and after Dose 14, biopsies, CVLs, and vaginal swabs will be collected to quantify concentrations of GRFT and CG (CVL); to measure antiviral activity in cell-based

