***Main study (Randomized period):***

Each subject will undergo screening up to 45 days prior to enrollment (Visit 0). If eligible, subjects will be seen in 9 additional scheduled visits.

At Visit 1/Enrollment (at least 7 days prior to the first dose), subjects will be enrolled and randomized to study product and to CVL time point, although no gel will be distributed at this visit. At this baseline visit, subjects will undergo a pelvic exam with 3 biopsies: 1 vaginal and 1 cervical biopsy for histology; and 1 cervical biopsy for transcriptome analysis (gene expression). Visit 1 will be scheduled to occur prior to the onset of menses (Menstrual Cycle Day 21-28 for women not on hormonal contraception; Hormonal Cycle day 15-22 for women on hormonal contraception) so that, ideally, the subject will have her menstrual period or withdrawal bleed after the biopsies and before she starts dosing.

At Visit 2 (Day 1), subjects will insert the first dose of their assigned study product in the clinic under direct observation, with a single PK assessment at 4 or 8 hours post-dose, at the same time they have the CVL collected; a swab for vaginal microbiome pre-dose; CVL collection pre-dose and 4h or 8h post-Dose 1 (based on randomization); and a baseline blood test for ADA. Visit 2 should be scheduled on Menstrual Cycle Day 7-10 for those not on hormonal contraception or Hormonal Cycle Day 1-4 for those on hormonal contraception, at least 7 days after Visit 1 to allow for sufficient time for healing, and to occur as soon as possible after menses

has ended. After Visit 2, subjects will continue using their product once daily for a total of 14 consecutive days.

At Visits 3, 4 and 5 (Days 3, 8 and 11), subjects will return to the clinic for outpatient blood draws to assess PK and safety. At those visits, subjects will insert their daily doses in the clinic after the blood draws. At Visit 4 (Day 8), a speculum exam will also be performed prior to insertion of the eighth dose.

At Visit 6 (Day 14), subjects will return to the clinic for the final dose of gel, PK sampling and ADA testing. After administering the final gel dose, subjects will remain in the clinic for up to 8 hours for PK blood draws.

At Visit 7 (Day 15), subjects will return to the clinic for a final (24 hour) PK blood draw and a pelvic exam with the same 3 biopsy specimens (2 cervical and 1 vaginal), CVL collection and a swab for vaginal microbiome.

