### 10.9.2 CVL and swab: drug concentrations, PD, immune mediators, anti-*E. coli* activity, and vaginal microbiome

CVLs will be collected to determine (1) GRFT and CG concentrations; (2) anti-HIV activity in cell-based assays and mucosal explants; (3) concentrations of genital tract immune mediators; (4) anti-*E. coli* activity; and (5) RSID testing to determine if condom-less sex occurred (NOTE: in the randomized portion of the study, the first RSID test will be done at enrollment using a swab instead of CVL). Each subject in the OL period will have 1 CVL collected at baseline (enrollment, before dosing) and 24h post-dose. Each subject in the randomized period will have 1 CVL collected at Visit 2/Day 1 before the first dose, after the first dose (at 4 or 8h, depending on stratification) and after the 14th dose (Day 15). Vaginal swabs will be collected from all subjects at before the first dose and following the last dose (Day 2 in the OL period; Day 15 in the randomized period) to determine if there are changes in the vaginal microbiome after GRFT administration.

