### 17.3 Determination of Sample Size

No formal sample size calculations were carried out for this study. A sample size of 20 subjects (14 active), allowing for a 10% drop out rate, is considered sufficient to evaluate the safety of PC-6500 and to assess the PK of GRFT.

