## 17.8 Statistical Analysis of Exploratory Endpoints

Concentrations of GRFT and CG in CVLs will be measured for each subject before and after the first dose. All subjects in the OL period will have CVLs collected 24h post-dose. In the main study, one-half of subjects will be randomized to CVL specimen collection at 4h after the first dose (n=10) and the other half will be randomized to CVL specimen collection 8h after the first dose (n=10). Mean concentration, minimum and maximum will be calculated and concentrations will be summarized for subjects sampled at the three different time points.

Log-normal generalized linear mixed models will be used to analyze changes between baseline and post-gel use in anti-HIV activity of CVL in explants and in concentrations of immune mediators in CVL.

Anti-HIV activity in CVL will be also assessed using a TZM-bl assay with the HIV-1ADA-M laboratory strain. Assays will be performed on serial dilutions to establish a dose-response curve. GraphPad Prism software will be used to prepare curve-fitting analysis and to calculate the median cytotoxicity concentration ( $CC_{50}$ ) and the half-maximal effective concentration values ( $EC_{50}$ , based on CVL dilution or drug concentrations) for all CVLs. Correlations between levels of GRFT in CVL and its anti-HIV activity will be calculated.

Transcriptome will be analyzed using Deseq2 and Voom software to evaluate statistical significance of changes in gene expression in tissue between baseline and post gel application.

Vaginal swabs will be collected to determine potential changes in microbiome post-gel exposure relative to pre-exposure. The unique fraction metric (UniFrac) will be used to measure the differences between microbial communities using the phylogenetic information. Linear discriminant analysis Effect Size (LEfSe) will be employed to compare the microbiome communities before and after gel application.

ADA will be assessed qualitatively both in baseline serum samples and in serum samples collected after daily GRFT use (Day 14), one week after the last gel application (Day 21) and two weeks after the last gel application (Day 28). Shift tables will be presented by treatment arm to summarize changes in detection of ADA between baseline and Days 14, 21 and 28.

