Mean E. coli inhibitory activity of CVL samples collected at baseline and at different time points after gel application will be calculated. Comparisons of the inhibitory activity of CVLs collected at different time points after gel application and versus CVL collected at baseline will be performed by paired t-tests or Wilcoxon-signed rank tests.

For all the computed PD parameters, number of observations, means, standard deviations, medians, and ranges will be presented by treatment arm and specimen collection time point.

RSID testing of CVLs or vaginal swabs will be done to determine if unprotected (condomless) sex occurred because semen could have an impact on some exploratory analyses. Specimens that test positive may be eliminated from some of the final analyses, to be further described in the SAP.

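### The tests named in Protocol 17.8 for exploratory endpoints compare before with after and state no PC-6500 versus PC-535 contrast, so for Day 15 lavage and swab endpoints a change can mix GRFT with vehicle and cycle timing

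*Protocol*

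**What the plan says.** The exploratory objectives (Protocol 6.2) ask about the impact of GRFT gel on gene expression, immune mediators and the microbiome, and of GRFT on anti-E. coli activity. The placebo, PC-535, is the carrageenan vehicle without GRFT (5.4).

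Section 17.8 names these comparisons:

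- **Explant anti-HIV activity and immune mediators:** "Log-normal generalized linear mixed models will be used to analyze changes between baseline and post-gel use in anti-HIV activity of CVL in explants"; the same sentence covers immune mediators in CVL.
- **Microbiome:** "Linear discriminant analysis Effect Size (LEfSe) will be employed to compare the microbiome communities before and after gel application". UniFrac measures distances between communities.
- **Gene expression:** DESeq2 and voom, for change in tissue from baseline to after gel use.
- **Anti-E. coli activity:** comparisons among post-gel time points and "versus CVL collected at baseline will be performed by paired t-tests or Wilcoxon-signed rank tests".

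The arms are reported separately in the descriptive statistics for every endpoint (17.2), the ADA shift tables and the summaries of PD parameters (both 17.8).

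On timing, 7.5 says: "Visit 2 should be scheduled on Menstrual Cycle Day 7-10 for those not on hormonal contraception". Women on hormonal contraception have Visit 2 on hormonal cycle day 1-4. Section 10.9.2 says: "Each subject in the randomized period will have 1 CVL collected at Visit 2/Day 1 before the first dose". The swab is also taken before Dose 1, and Section 12.3 and Appendix 2 agree on both. The synopsis says otherwise: "At baseline (at least 7 days before Dose 1) and after Dose 14, biopsies, CVLs, and vaginal swabs will be collected".

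On size, 17.3 says: "No formal sample size calculations were carried out for this study". It continues: "A sample size of 20 subjects (14 active), allowing for a 10% drop out rate".

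**The concern.** A randomised vehicle arm lets the effect of GRFT be separated from everything else that happens to a woman over two weeks of gel use. A before-after comparison does not use that information. Its change can contain a GRFT effect, a carrageenan effect, the passage from one part of the cycle to another and the effect of repeated lavage. Women on PC-535 are exposed to all of these except GRFT, so the difference in change between arms removes what is common.

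At stake is how the exploratory results are read. The trial is meant to inform other GRFT formulations (5.3), so a change in flora, mediators or E. coli inhibition that came from carrageenan or the cycle would mislead if carried forward as a property of GRFT. The protocol itself gives a reason to keep the vehicle in view: its macaque data suggested, without significance, that GRFT-carrageenan and carrageenan gels may act differently on some bacterial groups (5.2.3).

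Two further points concern how samples are matched. LEfSe is named for two samples from each woman with no provision for the pairing. The E. coli text names paired tests for comparisons among post-gel time points, yet each woman gives either a 4h or an 8h sample, never both.

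**Working it through.** **Stated sample size.** The protocol gives no calculation, so there is no power figure to reproduce. The split agrees with 7:3 allocation: 20 × 0.7 = 14 active and 20 × 0.3 = 6 placebo.

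**Cycle day at each sample.** Day 15 is 14 days after Visit 2 (Day 1).

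| Sample | Baseline | Day 15 | Matched? |
|---|---|---|---|
| CVL and swab, no hormonal contraception | Visit 2, day 7-10 | 7+14 to 10+14 = day 21-24 | No |
| CVL and swab, hormonal contraception | Visit 2, day 1-4 | 1+14 to 4+14 = day 15-18 | No |
| Cervical biopsy, no hormonal contraception | Visit 1, day 21-28 | day 21-24 | Yes |
| Cervical biopsy, hormonal contraception | Visit 1, day 15-22 | day 15-18 | Yes |

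The visit window of one day either way widens Day 15 to day 20-25 or 14-19, which does not alter the picture. The 4h and 8h CVLs are taken on the same day as their baseline, and the open-label CVL and swab 24h after dosing, so these are not phase-shifted.

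The first two rows depend on Visit 2 being the baseline. If the synopsis timing held, baseline CVLs and swabs would fall at about Visit 1 and would be roughly matched to Day 15.

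**Pairs available for E. coli activity.** Each randomised woman gives three CVLs: pre-dose, 4h or 8h, and Day 15. Baseline versus 4h, baseline versus 8h, baseline versus Day 15, and 4h or 8h versus Day 15 all have pairs. Only 4h versus 8h has none.

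**Illustration of a shared shift.** Assume no GRFT effect, a shift of d standard deviations (SD) of the change common to both arms, and a one-sample t-test of the change in the active arm at two-sided 5%. The level, the test and the shifts are assumptions; the documents give no size for a cycle or vehicle effect. The statistic is noncentral t with n − 1 degrees of freedom and noncentrality d√n. For n = 14 the critical value is 2.160.

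| d | d√14 | Rejection, n = 14 |
|---|---|---|
| 0.3 | 1.122 | 18% |
| 0.5 | 1.871 | 41% |
| 0.8 | 2.993 | 79% |

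Fourteen is a ceiling, because 9.4 says that enrolling all 20 women will not be feasible. With 10 active women (assumed; critical value 2.262) the rates are 14%, 29% and 62%. If the arms were pooled at n = 20, they would be 25%, 56% and 92%.

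**Active-minus-placebo contrast.** A shift common to both arms cancels, and the error rate stays at 5%. The 95% half-width, in SD of change, is t(0.975, n1+n2−2) × √(1/n1 + 1/n2):

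- 14 v 6: 2.101 × √(1/14 + 1/6) = 2.101 × 0.488 = 1.03.
- 12 v 5 (10% dropout: 12.6 and 5.4, rounded down): 2.131 × √(1/12 + 1/5) = 2.131 × 0.532 = 1.13.

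Power at 14 v 6 is 16% for a difference of 0.5 SD and 49% for 1.0 SD. The difference detectable with 80% power is 1.45 SD, or 1.60 SD at 12 v 5.

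**The case against.** The strongest reply is that the protocol does report by arm, in 17.2 and 17.8, so a shift common to both arms would be visible. A reader might infer that the placebo arm goes unused and that vehicle and phase effects are bound to be taken for GRFT effects. The documents do not support that. The arm is absent only from the named tests, and the by-arm summaries would give a careful reader warning. They do not, however, give an estimate of the difference in change with an interval.

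Second, 17.1 leaves detail to an SAP not at hand. Model terms in the mixed models and in DESeq2/voom properly belong there and could include arm. That stands, so their absence is not a fault in itself. What remains is that the protocol fixes the comparison as baseline versus post-gel for every one of these endpoints.

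Third, the exploratory endpoints (7.6, 17.5.2) are themselves mostly defined as changes from baseline, and objectives 3 and 4 speak of GRFT gel, not GRFT alone. Within-woman change does match the endpoint wording and may partly serve those two objectives. It still does not separate the gel from cycle timing, and objective 7 names GRFT.

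Fourth, a reader might infer that all samples are phase-shifted, or that the E. coli paired tests have no valid pairs. Neither holds: the exceptions are in the check above, and 17.8 does not itself name a 4h versus 8h comparison.

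Fifth, for anti-HIV activity the vehicle part is weak, since 5.2.2 reports no anti-HIV activity for carrageenan. That stands. Finally, 9.4 has the remaining women assigned case by case, so the between-arm contrast does not rest on strict randomisation throughout.

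**Conclusion.** The point holds in a limited form. The tests named in 17.8 are before-after, with no stated PC-6500 versus PC-535 contrast. For Day 15 immune mediators, anti-HIV activity, E. coli activity and the microbiome, baseline and follow-up lie 14 days apart in the cycle, so the named comparisons cannot by themselves separate GRFT from vehicle or cycle timing. Gene expression lacks the arm contrast only.

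The false-positive rates of 18%, 41% and 79% show the mechanism and are not forecasts. They rest on assumed shifts, a one-sample t-test standing in for the methods named, and the maximum of 14 active women. The phase argument also assumes that Visit 2 is the baseline, as 10.9.2, 12.3 and Appendix 2 state against the synopsis.

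The endpoints are exploratory, with no formal sample size behind them. This is an inexpensive improvement to the analysis and does not touch the primary safety and PK objectives.

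**What to change.** 1. In 17.8, state the estimate for these endpoints as change on PC-6500 minus change on PC-535, with a 95% confidence interval. Keep within-arm changes as descriptive.
2. Obtain it from an arm-by-time term in the log-normal mixed models, and from the same contrast in DESeq2/voom with woman as block. For the microbiome, compare woman-level changes between arms instead of relying on unpaired before/after LEfSe.
3. For E. coli activity, limit paired tests to samples from the same woman and treat any 4h versus 8h comparison as between women.
4. Reconcile the synopsis's baseline timing for CVLs and swabs with 10.9.2, 12.3 and Appendix 2.

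The cost is wording and analysis time; no visit or sample is added. The real price is precision: about 1.03 SD of change either way at 14 versus 6, and wider with fewer women. The planned placebo group is at most 3 per post-Dose 1 time point, so contrasts within 4h or 8h are weaker still. The arm contrast therefore supports estimation, not a firm test, and an interval that includes zero should not be read as absence of a GRFT effect.

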## 17.9 Exposure Analysis

Exposure to study drug will be measured as the total number of applicators used by subjects. The number of applicators inserted will be calculated as the total number of applicators inserted in the clinic (OL and randomized period) plus the number of applicators inserted at home (randomized period), per DSA testing. Exposure will be summarized by treatment group with means, standard deviations, medians, 1st and 3rd quartiles and ranges.

## 18. DATA HANDLING

### 18.1 Data Management Responsibilities

Study CRFs will be developed by the Population Council in conjunction with the study site. DataFax's electronic data capture (EDC) system will be used to record study data collected at the site on electronic case report forms (eCRFs).

The site will be responsible for entering the data electronically through the iDataFax application. Screening data should be entered as soon as possible and prior to enrollment. After enrollment, data should be entered within 7 days of each subject's visit. Periodically, the monitor will review study documents to verify compliance with the protocol. The accuracy of the data compared to source documentation will also be reviewed.

As a result of the data review process, corrections or changes to the data may be required. Discrepancies or questions concerning the data may be sent to the site in addition to queries that may be triggered during data entry of the eCRFs. The site will respond promptly to requests for clarifications and corrections.

### 18.2 Source Documents

The study site will maintain source data/documents in accordance with Population Council policy. The Investigator will maintain, and store securely, complete, accurate and current study records throughout the study. In accordance with US regulations regarding testing investigational products, the Investigator will maintain all study documentation for at least two years following the date of marketing approval for the study products being tested for the indication for which they were studied. If no marketing application is filed, or if the application is not approved, the records will be retained for two years after the investigation is discontinued and the US FDA is notified.

Study records must be maintained on site for the entire period of study implementation. Thereafter, instructions for record storage will be provided by the Council. No study records may be moved to an off-site location or destroyed prior to receiving approval from the Council.

## 19. CLINICAL SITE MONITORING

Study monitoring will be carried out by a Clinical Research Associate (CRA) contracted by the Population Council, or a Population Council staff monitor, in accordance with the current Council monitoring SOP. Monitoring visits will consist of a site initiation visit, periodic monitoring visits and a site close-out visit. Site visits will include the following:

- Review informed consent forms, subject eligibility, procedures, and documentation.
- Assess compliance with the study protocol, GCP guidelines, and applicable US regulatory requirements, including CFR Title 45 Part 46 and Title 21 Parts 50, 56, and 312.
- Perform 100% source document verification to ensure the accuracy and completeness of study data.
- Verify proper collection and storage of biological specimens.
- Verify proper storage, dispensing, and accountability of investigational study products.
- Assess implementation and documentation of internal site quality management procedures.
- The Investigator will allow study monitors to inspect study facilities and documentation (e.g., ICFs, clinic and laboratory records, other source documents, CRFs), as well as observe the performance of study procedures.
- The Investigator also will allow inspection of all study-related documentation by authorized representatives of the Population Council, FDA, OHRP and local and US regulatory authorities, IRBs and study staff.

A site visit log will be maintained at the study site to document all visits.

## 20. HUMAN SUBJECTS PROTECTION

The Investigator must ensure that each study subject, or her legally acceptable representative, is fully informed about the nature and objectives of the trial and possible risks associated with participation. The Investigator, or a person designated by the Investigator, will obtain written informed consent from each subject or the subject's legally acceptable representative before any trial-specific activity is performed. The ICF used in this trial, and any changes made during the course of the trial, must be prospectively approved by the relevant IRBs before use. The Investigator will retain the original of each subject's signed consent.

The site Investigator will make efforts to minimize risks to subjects. Before beginning the study, the Investigator will have obtained IRB approval and the Council will have submitted the protocol to the FDA. The Investigator will permit audits by the Council, FDA, OHRP and local and US regulatory authorities, IRBs and study staff or any of their appointed agents.

